## Plan for Sensitivity Analyses to Determine Impact of Key Assumptions

### Objective 1 and objective 2

As a sensitivity analysis, we will use a Generalized Estimating Equation (GEE) approach to analyze Objectives 1 and 2. Like MMRM, GEE is based on regression techniques and uses all data obtained from each participant. Potential advantages of GEE are that it is suitable for both continuous and dichotomous outcomes, and it does not require the correct specification of the variance–covariance structure. Additionally, GEE can be used to model data with nested structures by accounting for the correlation among outcomes for individuals in the same aggregate.

#### Objective 3

We will explore a multiple mediator model using structural equation modelling. The multiple mediator model posits a path model for each additional mediator and estimates a separate effect for each mediator. The significance of the mediation effects can be tested using a Sobel test based on an asymptotic approximation to the distribution of the indirect mediation effects [68, 69]. However, because this test is sensitive to sample size, as an alternative sensitivity analysis for mediation analyses, we also plan to use a non-parametric bootstrapping approach. Additional methods based on simulations will also be considered [70, 71].

#### Objective 4

A simultaneous assessment of mediator–moderator effects will be examined. We will examine mediated-moderation effects and moderated-mediation effects using strategies outlined by Fairchild and MacKinnon [72] and Hayes [73]. These strategies extend the mediator and multiple mediator models described under Objective 3 by adding a moderator effect and an interaction between treatment by moderator effect to the main models. Tests of significance for the individual moderator, mediator and interaction effects can be conducted using tests of joint significance and similar bootstrapping methods as for mediation effects.

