#### Objective 3 (Explore whether changes in parenting practices, family empowerment, and perceptions of team-based care mediate the effect of intervention on child outcomes)

We will examine whether changes in parenting practices, family empowerment, or perceptions of team-based care mediate the effect of treatment (PASS, TAU) on child outcomes. We will employ the method proposed by Hayes for examining mediation effects with regression modeling approaches, utilizing PROCESS macro [64]. The models will reflect change scores in the mediators. To produce a precise estimate of mediation effects and properly account for the potential of regression to the mean, baseline measurement of the mediator will be included as a covariate [64]. In each analysis, we assess mediation by first estimating the effect of the intervention condition (PASS, TAU) on the child outcome at post-treatment, while controlling for the influence of the mediator and estimating the direct effect of the intervention on child outcomes without the mediator. The mediation effect is the difference in estimated intervention effects between the models. If the difference is not equal to zero, then there is evidence of mediation of the intervention on child outcomes.

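### None of the sensitivity analyses committed to for Objective 3 varies the assumption that mediator and outcome errors are uncorrelated, so they could agree on a false mediator

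*Protocol article*

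**What the plan says.** The analysis section for Objective 3 compares the treatment coefficient on the child outcome with and without the mediator: "The mediation effect is the difference in estimated intervention effects between the models". A non-zero difference is taken as evidence of mediation. The mediator enters as a change score, and the one covariate named is its starting value: "baseline measurement of the mediator will be included as a covariate".

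A later section is headed "Plan for Sensitivity Analyses to Determine Impact of Key Assumptions". Under Objective 3 it lists:

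- a multiple-mediator model: "We will explore a multiple mediator model using structural equation modelling";
- a Sobel test: "The significance of the mediation effects can be tested using a Sobel test based on an asymptotic approximation";
- a bootstrap: "as an alternative sensitivity analysis for mediation analyses, we also plan to use a non-parametric bootstrapping approach". The reason given is "because this test is sensitive to sample size", with the Sobel test as the subject;
- an open item: "Additional methods based on simulations will also be considered".

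Four other places bear on this. The outcome sections make both primary outcomes parent ratings. The care-process section makes parenting practices, family empowerment and team-based care parent ratings too. The Concealment section says that parents know their assignment. The Sample size section labels the mediation analyses exploratory.

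**The concern.** An indirect effect is the product of two paths. Randomisation protects the path from treatment to mediator. It does not protect the path from mediator to outcome, because families are not randomised to mediator values. That path has a causal reading only if nothing unmeasured drives both mediator and outcome once treatment and covariates are accounted for; in a linear model this means uncorrelated errors.

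Here the assumption is fragile. A parent's mood, response style or family strain at 16 weeks can shift that parent's ratings of parenting practices and of child behaviour together. Adjusting for the baseline mediator removes part of a stable common cause, but not one that is new or that varies over time. Caregiver stress is measured at baseline for the subgroup work but is not named in the mediation model.

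The section's heading invites readers to take agreement among the listed methods as evidence that the key assumptions do not matter. On this assumption, agreement carries no such information, and an inert mediator could be reported as a mechanism that survived sensitivity analysis.

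**Working it through.** The plan states no power or error rate for Objective 3, so there is no figure to reproduce. The check has three parts.

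**1. What each listed analysis varies**

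- Sobel: a normal approximation to the standard error of the product of the two paths. Same point estimate.
- Bootstrap: a resampled distribution of that product. Same point estimate.
- Multiple-mediator model: adds the other measured mediators. It adjusts for anything they carry, but still sets the remaining mediator-outcome error correlation to zero.
- Simulation methods: only to be considered, and not described. A Monte Carlo interval for the same product would behave like the bootstrap.

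**2. Size when the mediator does nothing**

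Inputs from the Sample size section: 240 evaluable children (120 per arm), autocorrelation 0.3, and a PASS effect on care processes of a = 0.35 to 0.60 SD. Assumptions: true mediator-to-outcome path zero; residual correlation r of 0.1, 0.2 or 0.3; baseline mediator and baseline outcome both adjusted for, which is more than the plan names.

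With equal residual SDs, the estimated mediator-to-outcome path tends to r instead of 0, so the false indirect effect is a × r. At r = 0.2 it is 0.35 × 0.2 = 0.07 SD to 0.60 × 0.2 = 0.12 SD.

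How often both paths reach significance can be approximated by hand:

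- Residual SD of the mediator: √(1 − 0.3²) = 0.954. Standard error of a: 0.954 × 2/√240 = 0.123. So z = 0.35/0.123 = 2.84 (power 0.81) to 0.60/0.123 = 4.87 (power 0.998).
- For the mediator-to-outcome path, z = r√240/√(1 − r²): 1.56 at r = 0.1 (power 0.34), 3.16 at 0.2 (0.885), 4.87 at 0.3 (0.998).
- The product of the two powers approximates the rate of false mediation.

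Repeated simulations of 300–500 trials per cell, with 200–300 bootstrap resamples and a two-sided 5% level, agree. Ranges run over a = 0.35 to 0.60 and over runs:

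| Residual correlation | False indirect effect (SD) | Hand calculation | Bootstrap | Sobel |
|---|---|---|---|---|
| 0 | 0 | 4–5% | 3–8% | 1–4% |
| 0.1 | 0.035–0.06 | 28–34% | 25–38% | 11–29% |
| 0.2 | 0.07–0.12 | 72–88% | 69–89% | 46–85% |
| 0.3 | 0.105–0.18 | 81–100% | 79–100% | 71–100% |

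With three mediators in the outcome model, the bootstrap rates were 30–39%, 71–86% and 80–99% at 0.1, 0.2 and 0.3.

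**3. A different error structure, using the plan's own covariate**

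Here an unmeasured variable loads on post-treatment mediator and outcome, a = 0.45 SD, only the baseline mediator is adjusted for, and there are 200 trials per cell. The loadings are assumptions.

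| Loading | Sobel | Bootstrap | Two mediators, bootstrap |
|---|---|---|---|
| 0 | 1.5% | 7% | 7% |
| 0.3 | 13% | 22% | 20% |
| 0.5 | 64% | 75% | 65% |
| 0.7 | 84% | 88% | 85% |

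If the variable also affects the baseline mediator, the baseline covariate removes part of it. Bootstrap rates fall to 17%, 46% and 77% with one mediator, and to 15%, 35% and 54% with two. If PASS does not move the mediator at all (loading 0.5), every method stays between 0% and 3.5%.

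The methods err in the same direction, and the bootstrap flags the false mediator more often than Sobel.

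**The case against.** The strongest reply is that nothing in the section is false. A heading about key assumptions does not promise to test all of them, and the listed methods do vary two: the normal approximation, and one mediator against several. A correlation grid could be left to an analysis plan that is not shown. Part of this stands, since the heading is no guarantee of completeness. But the article itself names the analyses that serve as the sensitivity analyses, and the one assumption that randomisation cannot secure is not among those they vary. The simulation methods are not a commitment and cannot be judged from the documents.

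Exploratory status also stands as a limit. No primary or secondary treatment comparison is affected, and the plan makes no confirmatory mediation claim.

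Three stronger readings are tempting and not supported:

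- *That the methods would confirm a false mediator.* They could. PASS must move the mediator and the shared error must be material. At a correlation of 0.1 most simulated trials make no false claim, and no document figure fixes the correlation.
- *That the multiple-mediator model carries the full bias.* It can remove part: 77% fell to 54% in one scenario above.
- *That every Objective 3 result is exposed to shared parent error.* The plan speaks of child outcomes in general. Peer relationships and life satisfaction also have child-report versions, and some outcomes are teacher-rated. A parent's response style does not enter those ratings.

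**Conclusion.** The point holds as a limited one. The Objective 3 sensitivity analyses that the article commits to do not probe the mediator-outcome error correlation. For mediators and outcomes rated by the same unblinded parent, they could therefore agree on a false mediator. With the plan's own 240 children, autocorrelation of 0.3 and a 0.35–0.60 SD effect on the mediator, the bootstrap rate of false mediation is about 25–38% at a residual correlation of 0.1 and about 70–90% at 0.2. This rests on an assumed correlation, a linear model, and PASS moving the mediator as hypothesised. Because Objective 3 is exploratory, what is at stake is how a mechanism is described, not whether PASS is judged effective. The change is worth making but is not critical.

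**What to change.** In the sensitivity-analysis section under Objective 3, for each mediator-outcome pair:

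1. Re-estimate the indirect effect with the mediator-outcome error correlation fixed over a grid, for example −0.5 to 0.5.
2. Report the correlation at which the bootstrap interval first includes zero.
3. Describe any mediation finding as conditional on that value, and do not present agreement between Sobel and bootstrap as robustness to confounding.

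Do not turn the observed baseline mediator-outcome correlation into a pass/fail benchmark, attractive as that looks. It was tested with 240 children, autocorrelation 0.3, a 0.45 SD effect on the mediator and assumed path values. With real mediation and no confounding, fixing the error correlation at the baseline value cut detection from 92–96% to 5–6% (path 0.3) and from 79–81% to 8–9% (path 0.2). With no mediation and shared error arising only after baseline, it still declared mediation in about 57–87% of trials at correlations of 0.2 to 0.3. It performs well only when shared error is as large at baseline as later.

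The cost is a few sentences of plan text and some extra analysis of data already being collected. Some exploratory mediation claims will be stated less firmly.

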#### Determination of intervention effect sizes

To estimate the magnitude of the intervention effect, we will compute Cohen’s *d*. This statistic will be calculated as the ratio of between-group differences in changes in expected values over time divided by the standard deviation of the combined, unadjusted baseline scores for each outcome measure.

#### Data monitoring

The project statisticians will monitor data security on an ongoing basis. Oversight for data security and participant safety will be provided by a four-member Data and Safety Monitoring Board (DSMB). This board includes three senior-level faculty members, one of whom is a professor of biostatistics, and another who is a leader of our institution’s Research Family Partners Program and serves as a family advocate. This group will convene twice yearly. Included in its responsibilities, the DSMB can request an interim analysis to determine whether it is justifiable to continue the clinical trial, if questions about the rights and safety of participants arise.

#### Harms

The study team will inform the IRB of serious adverse events in a timely manner. Other adverse events will be documented in study records as directed by the IRB.

#### Auditing

The Office of Research Compliance at our institution audits study processes and procedures on an ongoing basis and is available to the study team for consultation as needed.

#### Protocol amendments

Amendments to the study protocol will be submitted to the IRB for review and approval.

#### Confidentiality

All data generated during this study will be kept confidential in accordance with institutional policies and HIPAA. Participants will be identified in the study database by an ID number. Electronic files holding the link between study ID number and identifying information will be kept in password-protected files kept on the secure study drive. The files linking study IDs and private health information will be retained for a minimum of 6 years post the data collection phase in accordance with our institution’s data retention policy.

#### Ancillary and post-trial care

Families who still need care after the study period will be able to continue with the integrated behavioral health provider in their primary care practice, or they will be referred for community-based services. If interim care is needed to address urgent issues, study clinicians will be available to provide support.

#### Dissemination policy

We will disseminate research methods and findings to researchers and practitioners in pediatrics, school and clinical psychology, and school mental health through presentations and publications in peer-reviewed journals. A summary of study results will be posted to the study website: https://www.research.chop.edu/partnering-to-achieve-school-success-study. Further, in collaboration with our institution’s Communications and Public Relations teams, we will publicize the results to families, teachers, and intervention providers through press releases and notifications on our institution’s Facebook pages and Twitter and LinkedIn feeds.

## Discussion

The major goal of this study is to evaluate the effectiveness of enhanced behavior therapy implemented in pediatric primary care tailored for families of children with ADHD who are economically marginalized. Enhancements include strategies to promote family engagement by involving Community Health Partners, a focus on distress tolerance to support caregivers in coping with chronic stress, team-based care involving collaboration between health and mental health clinicians, and strategies to promote effective family-school collaboration.

Strengths of the study include: (a) the intentional targeting of children and families who historically have been underrepresented in intervention trials; (b) examination of an intervention that has been uniquely tailored to address the needs of children and families marginalized by poverty who disproportionately belong to underrepresented racial/ethnic groups; (c) implementation of a clinical trial under conditions similar to authentic community-based practice; and (d) examination of outcomes important to the families of children with ADHD. In addition, this study will explore factors, such as parenting practices, family sense of empowerment to seek and obtain needed services, and caregiver perceptions of team-based primary care, that might explain in part the effect of intervention on child outcomes. Further, this study will examine whether there are differential effects of intervention based on socioeconomic factors and clinical characteristics of the child.

Outcomes of this study will be assessed using informant-report measures completed by parents, teachers, and children themselves. A practical challenge is that it can be difficult to obtain data from teachers. In some cases, caregivers might not provide consent for study team members to collect data from school personnel. In other cases, it might be difficult to connect with teachers and obtain their consent. Even when teachers are willing to participate, they might not complete measures, likely because of limited time and competing priorities when working in schools with limited resources. Nonetheless, we anticipate that we will have some success in collecting outcome data from teachers, which will enable our team to explore intervention effects on teacher-reported outcome measures.

Another practical challenge is that most of the behavioral health clinicians who will provide PASS work in large primary care practices with a high volume of referrals for behavioral health services. Although these clinicians often can provide brief same-day behavioral health care when children are seen for medical appointments, it can be difficult for them to offer follow-up care in a timely manner. By consenting to participate in this study, these behavioral health clinicians will agree to integrate PASS study cases into their busy schedules. By so doing, there might be constraints on how many appointments they can schedule with PASS patients during the 16-week intervention period.

The findings of this study will inform clinicians and researchers about how to provide psychosocial intervention in primary care to children with ADHD and their families who are economically marginalized. In addition, the study will identify strategies for overcoming barriers to providing evidence-based behavioral health services in pediatric primary care, informing more practical and sustainable models of care.

## Data Availability

The datasets and materials used during the current study are available from the corresponding author on reasonable request.
